**1. Road traffic injury**
a. Pedestrians should use zebra crossings to cross the road
b. Pedestrians should only cross the road when they see a green light
c. Even when accompanied by adults to cross the road, children should look left and right
d. Do not stand or play near parked or moving cars or trucks
e. Do not play near the road
f. Do not run, chase, skip, or jump when crossing the road
**2. Falls**
a. Be orderly and hold the handrail carefully when going up stairs
b. Do not climb or play at high places, such as tables, shelves, closets, cabinets, windows, and balconies
c. Hold the handrail carefully and do not jump, leap, or hurry down stairs. Also, do not crowd others.
d. Do not climb high trees, rocks, fences, or walls when playing outdoors
e. Do not push or shove other children when playing outdoors
f. Walk or run with caution, and do not stand in puddles or on rocks
**3. Drowning**
a. Never attempt to save a child who falls into the water by yourself or with other children
b. Seek adults for help when a person falls into the water
c. Learn what common objects can float on the water and might act as water rescue instruments
d. Never swim in or play around natural water by yourself or with other children but no supervising adults
e. Never swim without adult supervision
f. Wear safety floats while swimming if you do not know how to swim

For this study, the health effect of the Safety Experience Room intervention is the difference in the number of preschoolers experiencing unintentional injury events over the 12-month intervention period between the intervention and control groups. The costing of the intervention will include subsidies to the instructors paid from the project and costs for designing, furnishing and decorating each Safety Experience Room. The cost effectiveness ratio will be calculated as the total implementation costs of the intervention group divided by the health effect. Monte Carlo simulation (1000 runs using a truncated normal distribution) will be used to calculate a 95% uncertainty interval of the cost and outcome data.

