### Sample size

Based on a previous survey [28], we conservatively estimated that unintentional injury incidence among preschoolers aged 3–6 years old in the study sites over a 12-month period will be 30%. According to relevant reports [29], we estimated the effect size of the Safety Experience Room intervention will be 0.75 (incidence rate ratio) compared with a traditional educational intervention. An intra-class correlation (ICC) of 0.005 within a cluster size of 200 children per preschool was estimated [30, 31]. Nearly whole rural preschoolers stay enrolled in the same preschool throughout childhood, so we conservatively estimate a maximum attrition rate of 10% over the 12-month follow-up time period. Given these estimates, a minimum sample size of 2378 preschoolers is sufficient to achieve statistical power of 80% at the significance level of 0.05. Our preliminary surveys indicate most local rural preschools have 200 to 300 children, so 12 preschools will be adequate to recruit the needed sample size.

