### Intervention implementation

An operation manual was developed to ensure standardized implementation of the Safety Experience Room intervention. The manual consists of eleven chapters which together introduce the design, facilities, and class schedule for the Safety Experience Room intervention; elaborate the lessons that teachers deliver; specify strategies to evaluate the intervention’s effectiveness using the evaluation version of the interactive games; and inform the management and maintenance staff at the facilities about the teaching materials in the Safety Experience Room.

Along with distributing the operation manual, we will organize a standardized training session for all instructors involved in the intervention group to improve compliance with the operation manual and ensure all instructors implement the Safety Experience Room education and evaluation program in a standard way.

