## Outcome measures

### Primary outcome measure

The primary outcome measure will be the unintentional injury incidence rate among preschoolers over the 12-month study period, which will be calculated by combining data from the four follow-up evaluations. Follow-up evaluations will be conducted quarterly to minimize caregiver’s recall bias for minor or moderate injuries experienced by the child [34].

We define an injury event as an incident meeting any of three criteria: (1) child receives a medical diagnosis or treatment by a doctor or other medical professional following an injury; (2) child receives first aid, takes any injury-related medication, or receives massage or cold/hot compress by a family member, preschool teacher, preschool staff member, or other individuals following an injury; or (3) child is restricted from school or other activities, or is forced to stay in bed or rest for more than a half-day following an injury. If a caregiver reports that a child experienced more than one unintentional injury event in the prior 3 months, we will record the number of injury events and then collect specific information regarding the most severe one.

The unintentional injury incidence rate will be calculated as the “number of preschoolers who experience new unintentional injury events over the past year divided by the total number of preschoolers×100%”.

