### Secondary outcome measures

We will collect data concerning several secondary outcome measures, as detailed below.

Preschooler’s unintentional injury prevention knowledge for road traffic injury, falls, and drowning. This knowledge will be evaluated based on the learning content of the 6 educational themes children are exposed to in the Safety Experience Room. Table 3 lists 18 key items we will use to measure children’s unintentional injury prevention knowledge.Cost-effectiveness analysis (CEA). The calculation of CEA will follow the World Health Organization CHOosing Interventions that are Cost-Effective (WHO-CHOICE) approach to estimate population level effects of the interventions using a form of generalized cost-effectiveness analysis (GCEA) [35, 36].

**Table 3 Tab3:** Key unintentional injury prevention behaviors that preschoolers will learn for road traffic injury, falls, and drowning prevention

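### The cost-effectiveness health effect is an unscaled difference in numbers of injured children, so unequal arm sizes distort the ratio

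*Protocol article*

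**What the plan says.** Under Secondary outcome measures, in the text after Table 3, the protocol article sets the health effect as "the difference in the number of preschoolers experiencing unintentional injury events over the 12-month intervention period between the intervention and control groups". It continues: "The cost effectiveness ratio will be calculated as the total implementation costs of the intervention group divided by the health effect". For uncertainty it adds: "Monte Carlo simulation (1000 runs using a truncated normal distribution) will be used to calculate a 95% uncertainty interval of the cost and outcome data". No denominator, rate, per-child scaling or standardisation to a common arm size is stated. The reference to the WHO-CHOICE approach under the same heading does not supply one.

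The primary outcome is on a different scale. Under Primary outcome measure, the number of injured children is "divided by the total number of preschoolers×100", that is, expressed as a percentage.

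On arm sizes, four sections matter:
- Sample size plans on 200 children per preschool but reports that "most local rural preschools have 200 to 300 children".
- Preschool recruitment requires enrolment above 200, sets no upper limit, and allocates 6 preschools to each arm, 3 per county.
- Participant recruitment opens the study to every child at a participating preschool, subject to the exclusions, with no quota per preschool.
- Randomization and masking uses blocks of two preschools and mentions no matching on size.

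**The concern.** The numerator of the ratio is the cost of the intervention group. The matching denominator is the number of cases averted among the intervention-group children. The difference in counts equals that number only when the two arms hold the same number of children, and nothing in the design makes them equal. If the control arm is larger, extra injured control children are counted as cases averted. If the intervention arm is larger, real benefit is hidden. A programme with no effect can appear to avert injuries, and an effective one can show a health effect near zero, where the ratio explodes. The Monte Carlo step does not repair this: no correction for arm size is stated, so an interval built on the count difference is centred on the distorted value.

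**Working it through.** **Inputs.** From Sample size: control 12-month incidence 30%; incidence rate ratio 0.75, so intervention incidence 0.75 × 30% = 22.5%; ICC 0.005; cluster size 200; attrition 10%; power 80%; total 2378. From Data analysis plan: two-sided 0.05. From Table 2: $1967 per room.

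**The plan's own figure.** The article projects no health effect or cost-effectiveness ratio, so the sample size serves to confirm that the inputs are read correctly.
- Per arm, unpooled variance: (1.960 + 0.842)² × (0.30 × 0.70 + 0.225 × 0.775) / 0.075² = 536.34
- Design effect: 1 + 199 × 0.005 = 1.995
- Total: 2 × 536.34 × 1.995 / 0.9 = 2377.8, that is 2378. Reproduced.

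**Formulas.** Let nI and nC be the numbers of children in the intervention and control arms. The direction is taken as control minus intervention.
- Count difference, as written: 0.30 × nC − 0.225 × nI
- Cases averted in the intervention arm: nI × (0.30 − 0.225) = 0.075 × nI
- Quotient of the two: 4 × (nC / nI) − 3

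The multiplier of 4 is the point: near equality, each 1% difference in arm size shifts the health effect by about 4%.

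**Worked cases.**

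| nI | nC | Count difference | Cases averted | Quotient |
|---|---|---|---|---|
| 1200 | 1200 | 90 | 90 | 1.00 |
| 1200 | 1320 | 396 − 270 = 126 | 90 | 1.40 |
| 1320 | 1200 | 360 − 297 = 63 | 99 | 0.64 |
| 1400 | 1200 | 360 − 315 = 45 | 105 | 0.43 |
| 1600 | 1200 | 360 − 360 = 0 | 120 | 0 (ratio undefined) |

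Solving the quotient: the count difference is half the correct figure at nI/nC = 1.143, double at 0.80 and zero at 1.333.

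**No programme effect (30% in both arms).** The count difference is 0.30 × (nC − nI). With 1200 intervention and 1350 control children it is 45 cases apparently averted.

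**How likely.** The article gives no size distribution, so this step rests on an assumption: 12 preschool sizes, independent and uniform on 200 to 300. In 200,000 simulated allocations the quotient had median 1.00, middle half 0.82 to 1.19 and 95% range 0.51 to 1.56. It was 0.5 or less in about 2% of allocations, 1.5 or more in about 4%, and 2 or more in about 0.03%. Under no effect, each size has variance 100²/12 = 833.3, so nC − nI has SD √(12 × 833.3) = 100 children, and the 95% range of the count difference is 1.96 × 100 × 0.30 ≈ ±59 children.

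**Effect on the ratio, illustration only.** Room cost alone is 6 × $1967 = $11,802. At 1200 v 1320 the ratio is 11,802/126 = $94 as written against 11,802/90 = $131. At 1320 v 1200 it is 11,802/63 = $187 against 11,802/99 = $119. Total cost is not given, but any fixed cost would be distorted by the same factor.

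**The case against.** **Severity.** Only a secondary ratio is touched. The primary outcome is a proportion, the GEE and GLMM work on individual children, and the ratio could be rescaled later from data already collected. All of this stands, and it limits the severity.

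**Size.** A reader might infer that the health effect will routinely be halved or doubled. The calculation does not support that: halving is a tail event, the distribution centres on no distortion, and the uniform sizes are an assumption. The article says only that most preschools lie in that range, and it plans on 200 each.

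**How the number is estimated.** The article does not say the count will be a bare subtraction, and it invokes population-level effects under WHO-CHOICE. That leaves room for a better calculation, but the definition as stated contains no scaling.

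**Training cost.** A reader might infer that the numerator is understated. The costing lists "subsidies to the instructors paid from the project and costs for designing, furnishing and decorating each Safety Experience Room", while Intervention implementation says "we will organize a standardized training session for all instructors involved in the intervention group". The documents do not establish an omission: the list is introduced as what costing will include, which need not be exhaustive; the numerator is total implementation cost; and no training cost is given.

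**Attrition.** A reader might add differential dropout to the problem. The plan is intention-to-treat with imputation, and teachers follow up non-responders, so what remains is unequal enrolment.

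**Dissemination.** No cost-effectiveness threshold is stated, and roll-out also requires the programme to prove effective. A spurious count difference would not trigger it alone.

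**Conclusion.** The point holds as a defect in a stated definition; it should be fixed but does not threaten the trial. Followed as written, the rule gives a distorted cost-effectiveness ratio whenever the arms enrol different numbers of children, and the design leaves that to chance. The worked cases rest only on the article's 30% and 22.5% and the arm sizes shown. The statement of typical size (within about 20% in half of allocations, 0.51 to 1.56 at the 95% limits, about ±59 children under no effect) rests on the assumed uniform sizes and would change with the real enrolment figures. The main effectiveness analysis is not affected in this way.

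**What to change.** Redefine the health effect as the 12-month risk difference (control minus intervention) multiplied by the number of intervention-arm children. Scaling the control risk to the intervention arm's size is enough to remove the dependence on control-arm size: at these risks it gives 90 for nI = 1200 and 105 for nI = 1400 whatever nC is, and its expected value is zero if the programme does nothing. Preferably take the risk difference from the planned cluster-aware GEE or GLMM, so that the economic and effectiveness results agree, and draw the Monte Carlo runs from that estimate and its cluster-robust standard error.

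The cost is a few sentences of wording. It needs no new data, no change to randomisation and no change to sample size. It is best settled before arm sizes and outcomes are known, so that the choice of scale cannot be seen as driven by the result.

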**III. Learning evaluation**	
1. Evaluation tool	Evaluation version of the interactive games
2. Guidance material	Operation Manual of the Safety Experience Room

The Safety Experience Room will be flexibly divided into 3 zones, each with a specific function: a multi-media zone, a simulated scenario zone, and a spare zone (Fig. 3). The total cost of furnishing and decorating each Safety Experience Room will be controlled to a maximum cost of 13,200 CNY (approximately 1,970 USD), as detailed in Table 2.

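### As printed, the cost-effectiveness ratio is a first-year start-up figure: it sets the full one-off cost of reusable rooms against 12 months of effect

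*Protocol article*

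**What the plan says.** The cost-effectiveness paragraph belongs to Secondary outcome measures and stands below Table 3. It fixes three parts of the calculation:

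- Costs: the costing will include "subsidies to the instructors paid from the project and costs for designing, furnishing and decorating each Safety Experience Room".
- Effect: the "difference in the number of preschoolers experiencing unintentional injury events over the 12-month intervention period between the intervention and control groups".
- Ratio: "The cost effectiveness ratio will be calculated as the total implementation costs of the intervention group divided by the health effect".

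A Monte Carlo step of 1000 runs gives a 95% uncertainty interval for the cost and outcome data. Earlier in the same section the analysis is said to follow the WHO-CHOICE approach. The article gives no useful life, discount rate, annualisation or horizon beyond 12 months.

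Table 2 prices one room at $1,967: touchscreen computer and holder, shelves, chairs, instructor's furniture, props and mats. Table 1 describes six weekly lessons, with the full set given twice in one semester. The abstract, the Interventions section and the Discussion all link a favourable result to dissemination in rural China.

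**The concern.** The items in Table 2 outlast one year, and a course that fits into one semester can be repeated for later intakes in the same room. The printed formula nevertheless charges the whole purchase to the children spared an injury in the first 12 months. Cost and effect therefore run over different horizons.

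The trial names cost-effectiveness as one of its aims, and the Background makes affordability central to the case for the programme. Someone deciding on roll-out needs the cost per injured child averted once rooms are in use, as well as the cost of starting up. The printed ratio supplies only the second. The Monte Carlo interval, as described, varies cost and outcome data but not the horizon, so it would not show the difference.

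**Working it through.** **Inputs from the Protocol article.** Room cost $1,967 (Table 2); 6 intervention preschools (Preschool recruitment); control incidence 30%, ratio 0.75, ICC 0.005, cluster size 200, attrition 10%, 2378 children, 80% power, 0.05 (Sample size); two-sided tests (Data analysis plan); 1:1 allocation (Study design).

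**Assumed, not in the article.** Useful life, discount rate (3%), instructor subsidy per preschool-year, and effect after year 1.

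**1. The article's own figures reproduce.**
- Table 2: 776 + 102 + 81 + 120 + 58 + 597 + 233 = 1,967. The stated ceiling of 13,200 CNY / 6.70 = $1,970.
- Sample size: two proportions, 0.30 against 0.225, unpooled variance, give 536.34 per arm. Design effect 1 + 199 × 0.005 = 1.995. Then 2 × 536.34 × 1.995 / 0.90 = 2377.8, i.e. 2378.

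**2. Room equipment as the formula treats it.**
- Cost: 6 × 1,967 = $11,802.
- Injured children averted: 2378 / 2 × (0.30 − 0.225) = 1189 × 0.075 = 89.2.
- Ratio: 11,802 / 89.2 = $132. Counting only the 90% retained, 80.3 are averted and the ratio is $147.

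**3. The same equipment annualised, same effect each year.** Annual cost = K × r / (1 − (1 + r)^−L), with K = 11,802 and r = 3%.

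| Assumed life L | Annual cost | Per injured child averted | $132 divided by this |
|---|---|---|---|
| 3 years | $4,172 | $47 | 2.8 |
| 5 years | $2,577 | $29 | 4.6 |
| 8 years | $1,681 | $19 | 7.0 |

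**4. Adding the instructor subsidy.** With subsidy s per preschool-year, the first-year ratio is (11,802 + 6s) / 89.2 and the 5-year annualised ratio is (2,577 + 6s) / 89.2.

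| Assumed s | First-year | Annualised, 5 years | Factor |
|---|---|---|---|
| $250 | $149 | $46 | 3.3 |
| $1,000 | $200 | $96 | 2.1 |
| $2,000 | $267 | $164 | 1.6 |

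The factor falls below 2 once s exceeds 1,967 − 2 × (2,577 / 6), or about $1,110. Design cost is also one-off but lies outside Table 2. It would raise the dollar figures and move the whole-ratio factor back towards the equipment-only factor, never above it for the same life.

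**5. Relaxing the constant effect.** Suppose later benefit is confined to a newly enrolled third of pupils (an assumption based on three year-groups at ages 3–6). The undiscounted equipment-only factor is 1 + (L − 1) / 3, i.e. 1.7, 2.3 and 3.3 for 3, 5 and 8 years. If the full subsidy were also paid each year for that one-third effect, the later-year cost per child averted would be 6s / (89.2 / 3). This reaches the first-year ratio when 3s = 1,967 + s, so s is about $984. Beyond that, the whole ratio would no longer be overstated.

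**The case against.** The best case for the plan is that a within-trial, first-year ratio is legitimate and conservative. It uses the only effect the trial observes, and with the itemised budget published a reader can spread the room cost independently. The section also says the analysis will follow WHO-CHOICE, "using a form of generalized cost-effectiveness analysis (GCEA". That approach, or a fuller plan not shown, may annualise capital. All of this lowers the stakes. It does not remove the point, because the article goes on to print a formula for this study, and that formula does not annualise.

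A reader might infer from step 3 that the reported ratio will be several times too high. The documents do not support that. It would require start-up items to dominate the costs, and the subsidy, which is listed first, has no amount. Delivery is labour-intensive: with at most 30 children per session and more than 200 per preschool, at least 7 groups × 12 lessons = 84 sessions are needed if all take part. At a 5-year life, the $1,110 that brings the factor to 2 is only about $13 per session. The inference also needs the full first-year effect to recur. The Sample size section expects nearly all children to stay in the same preschool, so many pupils in year 2 will already have been taught.

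A reader might also infer that instructor training is left out of the costs. The article does commit to it ("we will organize a standardized training session for all instructors involved in the intervention group"), and the cost list does not name it. But that list is introduced as what the costing will include, the numerator is total implementation cost, and the training is described under Intervention implementation. A fair reading can cover it, so this is only a matter for clarification.

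**Conclusion.** The point stands in limited form and is minor, because it concerns a secondary outcome and leaves the primary analysis untouched. The printed ratio is a valid start-up figure. It is not the cost per injured child averted in a continuing programme, which is what roll-out also needs, and on room capital it errs upwards whenever the room has any effect after year 1.

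For equipment alone the figure is $132, against about $47, $29 or $19 at 3% over 3, 5 or 8 years. This rests on the protocol's planned effect and on the same effect recurring each year. For the whole ratio the overstatement is smaller, and its size cannot be fixed from the document. It may be under 2-fold, and under the least favourable combination in step 5 it could disappear.

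**What to change.** In the cost-effectiveness paragraph of Secondary outcome measures:

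- Separate start-up costs (design, furnishing, decoration) from recurrent costs (instructor subsidies).
- Keep the first-year ratio and label it as such. Report beside it an annualised ratio with a stated useful life and discount rate.
- Vary useful life and later-year effect in sensitivity analysis.
- State that instructor training counts as an implementation cost, and under which of the two heads it falls.

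This changes analysis wording only and needs no further data from children or caregivers. The downside is that the annualised ratio depends on an assumed useful life, which the trial cannot observe; reporting the range makes that dependence visible.

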### Data analysis plan

Primary data analysis will employ an intention-to-treat (ITT) approach. Descriptive statistics will be calculated for socio-demographic variables and primary and secondary outcomes, including mean (or median) and standard deviation (or range and interquartile range) for continuous variables, and frequency and proportion for categorical variables. At each time point, Chi-square test and two-sample t-test (or Wilcoxon rank sum test if data are skewed) will be used to examine the differences in outcome measures between intervention and control groups for categorical and continuous variables, respectively. Trend tests or analysis of variance (ANOVA) will be used to detect within-group differences across the four follow-up visits.

We will also use Generalized Estimating Equation (GEE) and Generalized Linear Mixed Models (GLMM) to evaluate the overall effectiveness of the intervention after adjusting for socio-demographic variables, engagement, and baseline injury events. Both binary outcomes (whether experienced unintentional injury during the study period) and quantitative count outcomes (number of unintentional injury events and injury prevention knowledge score) at the individual level will be analyzed using these models. Zero-inflation models will be used when needed.

Missing values will be imputed using either the Expectation Maximization (EM) algorithm or Markov Chain Monte Carlo, as appropriate for the data. A per-protocol (PP) sensitivity analysis will be conducted to validate ITT results. All statistical analyses will be performed using the up-to-date version of R. All statistical tests will be two-sided, with the level of 0.05 considered statistically significant.

Subgroup analyses will be performed to assess the impact of socio-demographic factors on the intervention effectiveness, including sex and age of children, grade level of preschoolers, education level of preschooler caregivers, and household income per capita in the prior 12 months. Subgroup analyses will follow the same statistical strategies for primary analyses.

This study will be rigorously conducted, analyzed, and reported in accordance with the Standard Protocol Items: Recommendations for Interventional Trials (SPIRIT) 2013 statement [37] and the Consolidated Standards of Reporting Trials (CONSORT) 2010 statement [38].

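### The planned cost-effectiveness ratio and its truncated-normal simulation cannot represent an effect near zero, and at the plan's own power the effect interval includes zero in about 1 trial in 5

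*Protocol article*

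**What the plan says.** The cost-effectiveness plan is in the protocol article under Outcome measures, Secondary outcome measures, in the paragraph after Table 3. The health effect is the difference between arms in the number of children with an unintentional injury over 12 months. The summary is then fixed: "The cost effectiveness ratio will be calculated as the total implementation costs of the intervention group divided by the health effect". Costs comprise instructor subsidies and the design, furnishing and decoration of each room.

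For uncertainty, a Monte Carlo simulation of 1000 runs from a truncated normal "will be used to calculate a 95% uncertainty interval of the cost and outcome data". The paragraph gives no truncation bound, does not say that the interval is for the ratio, and has no rule for an effect near or below zero.

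The Sample size section says that "a minimum sample size of 2378 preschoolers is sufficient to achieve statistical power of 80% at the significance level of 0.05". The Data analysis plan makes all tests two-sided at 0.05.

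**The concern.** A ratio with an uncertain denominator is well behaved only when that denominator is clearly away from zero. Here the denominator is the trial's own treatment effect on injured children. The trial is sized so that this effect is distinguishable from zero four times in five if the design assumptions hold, and less often if the effect is smaller. In the remaining trials cost divided by effect passes from very large positive values to negative ones as the effect crosses zero. A negative ratio does not say whether the programme is good or poor value.

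Cost-effectiveness is a stated aim and a named secondary outcome. The Discussion makes wider dissemination depend on the programme proving effective and economically feasible. A cost per injured child averted that looks finite and positive whatever the trial found could mislead that decision.

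**Working it through.** **Inputs.** Control risk 0.30, ratio 0.75 (so 0.225), ICC 0.005, cluster size 200, attrition 10%, power 0.80, two-sided 0.05 (Sample size; Data analysis plan). Room cost $1,967 (Table 2), 6 intervention preschools (Preschool recruitment). Subsidies and design costs are not given, so cost is taken as fixed at 6 × 1,967 = $11,802, for illustration only.

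**1. The plan's sample size.**
- Per arm, unpooled variance: (1.960 + 0.842)² × (0.30×0.70 + 0.225×0.775) / 0.075² = 536.34.
- Design effect: 1 + 199×0.005 = 1.995.
- Total: 2 × 536.34 × 1.995 / 0.90 = 2377.8, which rounds up to 2378. The plan's figure reproduces exactly, so its power is 80% on its own inputs.

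**2. The denominator at the design effect.** About 2378 × 0.9 / 2 = 1070 children are analysed per arm.
- Effect = 1070 × 0.075 = 80.3 injured children averted.
- SE = √(1070 × 0.384375 × 1.995) = 28.6.
- 95% interval: 80.3 ± 1.96×28.6 = 24 to 136.
- Ratio: 11,802/80.3 = $147, with limits 11,802/136.4 = $87 and 11,802/24.1 = $490.
- Probability that the effect interval includes zero: Φ(1.96 − 80.25/28.64) = Φ(−0.84) = 0.20.
- The estimate itself is zero or negative in only Φ(−2.80) = 0.25% of trials.

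The 20% becomes 17.9% if the cluster size falls to 178 after attrition, and 26% to 29% with a t reference on 10 degrees of freedom for 12 preschools.

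**3. A smaller true effect (risk ratio 0.85, assumed).**
- Effect = 1070 × 0.045 = 48.2; SE = √(1070 × (0.21 + 0.255×0.745) × 1.995) = 29.2; 95% interval −9 to 105.
- Probability that the effect interval includes zero: Φ(1.96 − 1.648) = 0.62.

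**4. What the simulation gives if draws may cross zero.** Take draws centred on the effect in step 3. The share below zero is π = Φ(−1.648) = 0.0497.
- Lower 2.5% of the ratio: the effect value with cumulative probability 0.0497 − 0.025 = 0.0247, which is −9.27. The ratio is 11,802/(−9.27) = −$1,270.
- Upper 2.5%: the effect value with cumulative probability 0.0497 + 0.025 = 0.0747, which is 6.02. The ratio is 11,802/6.02 = $1,960.

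The lower end comes from draws showing harm, so the range does not run from good value to poor value.

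**5. What it gives if draws are truncated at zero.** Quantiles of the effect are e + SE × Φ⁻¹(π + p(1 − π)).
- Effect of step 3: about $111 to $2,050, although the effect interval is −9 to 105.
- Observed effect exactly nil (30% in both arms): SE = √(1070 × 0.42 × 1.995) = 29.94. The median draw is 0.6745 × 29.94 = 20.2, and 11,802/20.2 = $584. The 2.5% and 97.5% points of the effect are 0.94 and 67.1, giving $12,600 and $176.

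Without truncation, the same nil result gives a probability of 1 − Φ(20.2/29.94) = 0.25 that the programme costs less than $584 per injured child averted. With truncation at zero it is 0.50, because all draws showing harm have been removed.

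**The case against.** The strongest reply has four parts.

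- **The ratio's distribution is available.** The sentence on simulation directly follows the definition of the ratio, and joint runs of cost and outcome are the natural way to get its distribution. The wording may simply be loose, and a condensed article may leave that step to the analysis plan. This stands: a reader might infer that the ratio would be left with no usable uncertainty, but the same draws can be divided. Even on the literal reading, the effect interval would be reported.
- **The plan specifies truncation.** A reader might infer that the planned interval is itself infinite in 1 trial in 5, or that the problem is the same wherever the normal is cut. The document supports neither. The 20% describes a valid untruncated or Fieller-type interval. With truncation at zero every limit is finite: this was so in all 4000 simulated trials at the design effect. But the fault then changes form, as step 5 shows: no effect and harm are ruled out in advance.
- **Roll-out does not hang on the ratio alone.** Effectiveness is also required, and where the effect interval includes zero that condition would probably fail anyway. This is fair and limits the consequence, but the published cost-effectiveness figure would still mislead.
- **The dollar amounts are incomplete.** This is also fair. They omit subsidies and design costs and treat cost as fixed. The 20% and 62% do not depend on them.

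**Conclusion.** The point holds in a limited form. The article fixes a ratio whose denominator has a 95% interval including zero in about 20% of trials at the design effect, and in 62% at an assumed risk ratio of 0.85. It pairs this with a truncated-normal simulation that has no stated bound. Neither possible bound handles those trials: draws that cross zero give an interval that cannot be ordered, and draws cut at zero give a finite positive cost per child averted even when the observed effect is nil.

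The size rests on the plan's risk, ICC, cluster size and attrition, equal arms and a normal approximation. A larger ICC would raise the 20% (34% at 0.01 and 54% at 0.02, both assumed, with cluster size 178). It is a secondary outcome, so the primary result is unaffected.

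**What to change.** Amend the cost-effectiveness paragraph, or the analysis plan, as follows:

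- Keep cost divided by effect as a point summary.
- Draw cost and effect jointly. Take the effect and its standard error from the preschool-clustered analysis, and do not truncate the effect at zero. State any bound used for cost.
- Report incremental net benefit (value per injured child averted × effect − cost), or the probability that the programme costs less than a given amount per injured child averted, over a range of amounts stated in advance. Both remain valid when the effect is near or below zero.
- Give a Fieller-type interval for the ratio only when the 95% interval of the effect excludes zero. Otherwise report incremental cost and incremental effect separately, each with its interval.

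This takes a few sentences and a few lines of code, with no new data. The downside is small: a range of values per injured child averted has to be chosen, and the result is less simple than one number.
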